## Statistical analysis

4

All analyses were conducted according to the intention-to-treat (ITT) principle. The full analysis set (FAS) included all participants who were randomized and received at least one session of treatment. Statistical analyses were performed using SPSS Statistics software (version 26.0). Continuous variables were tested for normality using the Shapiro–Wilk test. Normally distributed data are presented as mean ± standard deviation (SD), whereas non-normally distributed data are expressed as median (interquartile range, IQR). Between-group comparisons were performed using the independent-samples t-test or Mann–Whitney U test, as appropriate. Within-group comparisons were conducted using the paired t-test or Wilcoxon signed-rank test. Categorical variables were analyzed using the Chi-square test. Pearson or Spearman correlation analyses were performed, as appropriate, to evaluate the correlations of SCFAs, HDAC1, and pS129-*α*-syn levels with CCS scores.

Repeated-measures data were analyzed using linear mixed-effects models (LMMs). Fixed effects included group, time, and the group-by-time interaction. Predefined covariates comprised age, sex, disease duration, and levodopa equivalent daily dose (LEDD). Participant-specific random intercepts were included as random effects. The covariance structure for repeated measures was selected based on the Akaike Information Criterion (AIC) and Bayesian Information Criterion (BIC), and the optimal covariance structure was used for model estimation. If the group-by-time interaction was statistically significant, *post hoc* multiple comparisons were performed with Bonferroni correction, and the results were presented as least squares mean differences (LSMDs) with 95% confidence intervals (CIs). Sensitivity analyses, including complete-case analysis and multiple imputation, were conducted to evaluate the impact of missing data on the robustness of the findings. No adjustment for multiple comparisons was applied for exploratory endpoints, including SCFAs, HDAC1, and pS129-*α*-syn; therefore, these findings should be interpreted cautiously pending further validation. All statistical tests were two-sided, and *p* < 0.05 was considered statistically significant.

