### Trial design and setting

2.1

This prospective randomized controlled trial was conducted in accordance with the principles of the Declaration of Helsinki and was developed in compliance with the Standard Protocol Items: Recommendations for Interventional Trials (SPIRIT) 2025 checklist (Chan et al., 2025). The trial is scheduled to be conducted from February 2026 to May 2027 at the outpatient acupuncture clinic of the First Affiliated Hospital of Guangzhou University of Chinese Medicine. The trial protocol has been approved by the hospital’s ethics committee (approval number: JY2025-164) and has been registered with the International Traditional Medicine Clinical Trial Registry (registration number: ITMCTR2026000107).

A total of 66 eligible participants will be recruited from the acupuncture outpatient department. After providing written informed consent, participants will be randomly assigned in a 1:1 ratio to one of two parallel groups: the real acupuncture group (*n* = 33) or the sham acupuncture group (*n* = 33). The intervention period will last for 8 weeks. Outcome assessments will be conducted at baseline, after the 4-week intervention, and after the 4-week follow-up. A flowchart illustrating the trial design is presented in Figure 1.

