### Sample size calculation

2.3

The primary outcome of this trial is the Chronic Constipation Severity Scale (CCS) score. Sample size estimation was based on data from a previous randomized controlled trial investigating acupuncture for patients with PD–related constipation (Lei et al., 2020; Zhen et al., 2021). In that trial, the mean CCS score after acupuncture treatment was 8.79 with a standard deviation (SD) of 4.63, whereas the control group showed a mean CCS score of 12.36 with an SD of 4.26. Sample size calculation was performed using PASS 2021 software, using a superiority test to compare two independent means. The significance level was set at *α* = 0.05 (two-sided), and the statistical power was 80% (1 − *β* = 0.80). Based on these assumptions and an anticipated 20% dropout rate, a total sample size of 66 participants was required to detect a statistically significant superiority in CCS scores between the two groups after the intervention. The sample size was powered for the primary clinical endpoint only.

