### Outcomes assessment

2.7

Outcome evaluation primarily focused on two domains: constipation severity and other PD-related outcomes. Clinical scale assessments and the collection of fecal and blood samples were conducted at three time points: pre-treatment (baseline), after week 4 of the treatment period, and at week 4 of the follow-up period (Table 2). All assessments and biospecimen collections were performed during the participants “on” medication state at each visit. Outcome assessors received standardized training and remained blinded to group allocation throughout the trial.

**Table 2 tab2:** Details of the planned visit schedule.

Task	Baseline period	Treatment period				Follow-up period
	Week 0	Week 1	Week 2	Week 3	Week 4	Week 8
Enrollment						
Informed consent	√					
Random assignment	√					
Demographic characteristics	√					
Intervention						
Real acupuncture		√	√	√	√	
Sham acupuncture		√	√	√	√	
Assessments						
CCS	√				√	√
CSBMs and SBMs	√				√	√
BSS	√				√	√
UPDRS	√				√	√
SCFAs	√				√	√
HDAC1 and pS129-α-syn	√				√	√
Blinding assessment		√			√	
Safety						
Adverse events		√	√	√	√	√

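### The only analysis named for the biomarker–CCS association is a plain correlation of levels, which takes account of neither randomised arm nor the three repeated visits

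*Protocol article*

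**What the plan says.** The association between biomarkers and symptoms has one sentence in section 4, Statistical analysis, of the protocol article: "Pearson or Spearman correlation analyses were performed, as appropriate, to evaluate the correlations of SCFAs, HDAC1" and pS129-α-syn "levels with CCS scores". No visit, arm adjustment, change score or repeated-measures version of the correlation is given.

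Section 2.7, Outcomes assessment, states that the clinical scales and the stool and blood sampling "were conducted at three time points: pre-treatment (baseline), after week 4 of the treatment period, and at week 4 of the follow-up period". Table 2 lists CCS, SCFAs, HDAC1 and pS129-α-syn at all three. Section 2.1 has participants "randomly assigned in a 1:1 ratio to one of two parallel groups", 33 in each.

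The next paragraph of section 4 says "Repeated-measures data were analyzed using linear mixed-effects models (LMMs"), with group, time, their interaction, four baseline covariates and a random intercept. The biomarker is not among the predictors, so that model does not estimate the biomarker–CCS association.

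Section 2.7.3 calls all biomarker analyses exploratory and hypothesis-generating. Section 4 asks for caution because multiplicity is not adjusted for. The Discussion says that causal relations between biomarkers and outcomes cannot be established.

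**The concern.** The p-value of a Pearson or Spearman correlation assumes independent pairs, and the coefficient describes a single population. These data break both conditions unless the analysis is restricted or adjusted.

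- **Visits pooled.** Three records from one person are not three independent records, so the standard error is too small.
- **Arms pooled after treatment.** If acupuncture lowers CCS and also moves a biomarker, the two arm means alone produce a correlation, even when patients within an arm show no relation.
- **Levels instead of changes.** The Discussion describes the samples as a way to quantify biomarker change after acupuncture. A correlation of levels mixes stable differences between people with change within people.

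At stake is the exploratory mechanistic reading. A significant coefficient could be reported as a biomarker tracking symptoms when it reflects only repeated records or the treatment contrast.

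**Working it through.** **Inputs from the article.** 33 per arm; three visits; two-sided 5% level; 80% power; 20% dropout. For CCS, "the mean CCS score after acupuncture treatment was 8.79 with a standard deviation (SD) of 4.63", against 12.36 (SD 4.26) in the control group.

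**Inputs assumed, because the article gives none.** ICC across visits (taken as equal for CCS and biomarker) and biomarker shift under real acupuncture, both shown as ranges.

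**1. The plan's own figure.** Difference = 12.36 − 8.79 = 3.57. Pooled SD = √((4.63² + 4.26²)/2) = 4.449. Standardised effect = 3.57/4.449 = 0.80. With the noncentral t, 26 per arm gives power 0.810 and 25 gives 0.794. Then 26/0.8 = 32.5, so 33 per arm and 66 in total, which matches "a total sample size of 66 participants was required". The 0.80 SD effect is used below.

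**2. Visits pooled, no treatment effect, no true association.** For two unrelated variables with the same ICC over three visits, the variance of r is inflated by about 1 + (3 − 1) × ICC². The real size of the nominal 5% test is then 2 × [1 − Φ(1.96/√inflation)].

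| ICC | Inflation | 1.96/√inflation | Size by formula | Simulated, 198 records |
|---|---|---|---|---|
| 0.3 | 1.18 | 1.804 | 7.1% | 7.0% |
| 0.4 | 1.32 | 1.706 | 8.8% | – |
| 0.5 | 1.50 | 1.600 | 11.0% | 10.1% |
| 0.7 | 1.98 | 1.393 | 16.4% | 16.7% |
| 0.8 | 2.28 | 1.298 | 19.4% | – |
| 0.9 | 2.62 | 1.211 | 22.6% | 23.2% |

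Over ICC 0.4–0.8 the size is about 8–20%; other simulations with 52–66 participants gave 8.2% to 19.8% over that range.

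**3. Arms pooled at one post-treatment visit, no relation within either arm.** With CCS effect d = 0.80 and biomarker shift b, both in SD units, the induced correlation is |r| = (d·b/4)/√[(1 + d²/4)(1 + b²/4)].

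| b (SD) | Induced abs(r) | Significant, 33 per arm | Significant, 26 per arm |
|---|---|---|---|
| 0 | 0 | 4.8% | 5.0% |
| 0.3 | 0.055 | 7.5% | 6.9% |
| 0.5 | 0.090 | 11.0% | 9.5% |
| 0.8 | 0.138 | 20.6% | 16.7% |
| 1.0 | 0.167 | 27.5% | 22.3% |

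The last two columns are simulated. Check by Fisher's z for b = 0.8 and 66 patients: √63 × atanh(0.138) ≈ 1.10, so the chance of significance is about Φ(1.10 − 1.96) + Φ(−1.10 − 1.96) ≈ 0.20.

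**4. Both pooled, ICC 0.5.** Simulated rates are 15.3%, 26.2% and 44.2% for b = 0.3, 0.5 and 0.8.

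**5. Readings that keep the 5% level.** A single visit within one arm, or baseline only, is valid. Splitting by arm and visit leaves 26–33 pairs per test. Counting SCFAs as one variable, and HDAC1 and pS129-α-syn each in stool and blood, that is 5 × 2 × 3 = 30 tests, with about 30 × 0.05 = 1.5 false positives expected if nothing is related.

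**6. Remedies checked by simulation, 33 per arm.**
- Partial correlation of the baseline-to-week-4 changes, adjusted for group: 4.7–5.2% for ICC 0.6 with b = 0.3–0.8, and for ICC 0.8 with b = 0.8.
- Within-person association with group and visit main effects only: at ICC 0.6, about 8%, 14% and 27% for b = 0.3, 0.5 and 0.8; at ICC 0.8 and b = 0.8, about 70%.
- The same with group-by-visit added: 4.7–5.0%.

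Treatment acts only after baseline, so main effects of group and visit cannot absorb it; the interaction can.

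**The case against.** The strongest reply is that no pooling is stated. A correlation within one arm at one visit, or at baseline, is valid, and a journal article may leave that choice to a fuller document. The mixed-model paragraph also suggests that the authors know repeated records need their own method. This stands in part. A reader might infer that the analysis disregards arm and visit, and the text does not support going that far. What the article does fix is the method and the use of levels, and the mixed model it describes contains no biomarker term. The suggestion is therefore to replace a stated method with a better one, and not merely to fill in a detail.

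A reader might also infer that these correlations will be taken as proof of a gut–brain mechanism. The article says otherwise in three places: exploratory status (section 2.7.3), caution (section 4) and no causal conclusion (Discussion). Those statements limit the consequence. They concern power, multiplicity and causality, however, and none mentions dependent records or confounding by arm.

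Two further points are fair. The calculated rates depend on ICCs and biomarker shifts that the article does not give, and with no biomarker shift, pooling arms at one visit stays near 5%. And where treatment truly moves both variables, the marginal correlation is not zero, so the excess in that case is a problem of interpretation more than of test size.

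**Conclusion.** The point holds in a limited form. The one method named for the biomarker–CCS association does not account for arm or for repeated visits. If visits are pooled, the real error rate is about 8–20% for ICCs of 0.4–0.8. If arms are pooled at week 4, about 10–21% of tests are significant without any within-arm relation, given the planned 0.80 SD effect on CCS and a biomarker shift of 0.5–0.8 SD. Pooling, the ICCs and the biomarker shifts are all assumptions. The induced correlation is modest. Nothing here touches the primary outcome, the sample size or the clinical secondary outcomes. It is an improvement to an exploratory analysis and not a threat to the trial's main conclusion.

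**What to change.** Replace the plain correlation of levels with one of the following, and state the visit or visits used.

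1. The partial correlation of change from baseline in the biomarker with change from baseline in CCS, adjusted for group, on the raw values or on ranks.
2. The planned linear mixed model for CCS with the biomarker added, split into each person's mean and the deviation from that mean, keeping group, visit and the group-by-visit interaction. The interaction must stay in, otherwise the treatment-induced association remains in the within-person coefficient.

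Either needs a few lines of SPSS and no new data. The cost is a result slightly harder to present than a single correlation coefficient.

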**Methods:**

This randomized controlled clinical trial will enroll 66 patients with PD–related constipation and randomly assign them in a 1:1 ratio to the real acupuncture group or the sham acupuncture group. Participants, acupuncturists, outcome assessors, and statisticians will be blinded to group allocation. The 8-week trial consists of a 4-week treatment period followed by a 4-week follow-up period. The primary outcome is the longitudinal change in the Chronic Constipation Severity Score (CCS) over time. Secondary clinical outcomes include weekly complete spontaneous bowel movements (CSBMs), spontaneous bowel movements (SBMs), Bristol Stool Scale (BSS) scores, and Unified Parkinson’s Disease Rating Scale (UPDRS) scores. In addition, exploratory outcomes include levels of short-chain fatty acids (SCFAs), histone deacetylase 1 (HDAC1), and phosphorylated *α*-synuclein at serine 129 (pS129-α-syn) measured in biofluid samples. Adverse events will be systematically monitored throughout the trial. The study is conducted in accordance with the SPIRIT guidelines.

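### The CCS mixed model is valid, but it does not adjust for baseline CCS; adjusting would sharpen the estimate using data already collected

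*Protocol article*

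**What the plan says.** The abstract defines the primary endpoint: "The primary outcome is the longitudinal change in the Chronic Constipation Severity Score (CCS) over time". Section 2.7 and Table 2 place the CCS assessments at "pre-treatment (baseline), after week 4 of the treatment period, and at week 4 of the follow-up period", so baseline is one of three measurements of the outcome.

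Section 4 gives the analysis: "Repeated-measures data were analyzed using linear mixed-effects models (LMMs"). On the model terms it says "Fixed effects included group, time, and the group-by-time interaction", "Participant-specific random intercepts were included as random effects", and "Predefined covariates comprised age, sex, disease duration, and levodopa equivalent daily dose (LEDD"). Baseline CCS is not in that list, and nothing says that the arms share a baseline mean. If the interaction is significant, Bonferroni-corrected comparisons follow and "the results were presented as least squares mean differences (LSMDs) with 95% confidence intervals (CIs"). Section 4 does not say whether the reported difference is the gap between arms at week 4 or the gap in change from baseline.

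**The concern.** The article states the fixed effects and the covariate list outright, so this is a choice made in the document and not a detail left for later.

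With a group main effect, a full group-by-time interaction and baseline as a response, each arm has its own baseline mean. The model can then give two kinds of treatment estimate:

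- **Difference in change from baseline** (the interaction contrast). It subtracts the whole baseline difference, which over-corrects unless the correlation is 1.
- **Difference between arms at week 4.** It does not correct for baseline CCS at all.

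Neither uses the fact that randomisation makes the true baseline means equal. A model that uses it is at least as precise as both at any correlation from 0 to 1, apart from a negligible cost in degrees of freedom. At stake are the width of the confidence interval and how far a chance difference at baseline carries into the result of a 66-patient trial. Validity is not at stake.

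**Working it through.** **Inputs from section 2.3.** For the acupuncture arm, "the mean CCS score after acupuncture treatment was 8.79 with a standard deviation (SD) of 4.63"; the control figures are 12.36 (SD 4.26). The difference is 12.36 − 8.79 = 3.57. The pooled SD is √((4.63² + 4.26²)/2) = 4.449. The test is two-sided at 0.05 with 80% power and 20% dropout.

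**The plan's own figure.** A two-sample t-test at effect size 3.57/4.449 = 0.802 needs 25.4 per arm, so 26. Then 26/0.80 = 32.5, so 33 per arm and 66 in total. The stated size reproduces.

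**Assumptions added here.** The article gives post-treatment SDs only, so the baseline SD is assumed equal to 4.449. The correlation ρ between baseline and week 4 is not given; 0.3, 0.5 and 0.7 are shown. Pairs are complete, and the four listed covariates are taken to add no precision.

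**Variance, in units of the post-treatment variance**

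- Unadjusted week-4 difference: 1
- Difference in change: 2(1 − ρ)
- Baseline-adjusted or common-baseline estimate: 1 − ρ²

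The ratios to the adjusted estimate are therefore 1/(1 − ρ²) for the week-4 difference and 2(1 − ρ)/(1 − ρ²) = 2/(1 + ρ) for the change.

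| | ρ = 0.3 | ρ = 0.5 | ρ = 0.7 |
|---|---|---|---|
| Variance ratio, change | 1.54 | 1.33 | 1.18 |
| Variance ratio, unadjusted week 4 | 1.10 | 1.33 | 1.96 |
| SE, change (26 per arm) | 1.46 | 1.23 | 0.96 |
| SE, unadjusted week 4 | 1.23 | 1.23 | 1.23 |
| SE, baseline-adjusted | 1.18 | 1.07 | 0.88 |
| Power, change | 67% | 81% | 96% |
| Power, unadjusted week 4 | 81% | 81% | 81% |
| Power, baseline-adjusted | 84% | 91% | 98% |

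Each SE is 4.449 × √(variance factor) × √(2/26). The powers come from the noncentral t for one week-4 contrast of 3.57 points at the 5% level. They illustrate relative precision and are not the power of the planned interaction test.

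**Chance imbalance.** With 33 per arm, the SE of the baseline difference is 4.449 × √(2/33) = 1.095. Its 95% range is ±1.96 × 1.095 = ±2.15 points. Each point of imbalance shifts the week-4 difference by +ρ and the change contrast by −(1 − ρ). At the edge of the range:

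| | ρ = 0.3 | ρ = 0.5 | ρ = 0.7 |
|---|---|---|---|
| Shift in week-4 difference | ±0.64 | ±1.07 | ±1.50 |
| Shift in change contrast (opposite sign) | ∓1.50 | ∓1.07 | ∓0.64 |

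**Check by simulation.** In 20,000 simulated trials per correlation with 33 per arm, the slopes of the estimate on baseline imbalance were 0.31, 0.49 and 0.70 for the week-4 difference. They were −0.69, −0.51 and −0.30 for the change contrast, and about 0 with adjustment. All three estimators averaged close to the true difference of 3.57.

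**The case against.** The strongest reply is that nothing here is an error. A mixed model with baseline among the responses is a standard analysis. It is unbiased under randomisation, and its standard error already includes the variation from chance imbalance, so type I error and coverage are as stated. Baseline is also not ignored, because the interaction compares changes from it. All of this stands. What remains is that the same data would give a more precise answer.

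The least favourable figures also need opposite conditions: 67% power for change requires ρ = 0.3, while the ratio of 1.96 for the week-4 difference requires ρ = 0.7. They cannot both apply. If baseline predicts later CCS strongly, the change contrast loses little (96% against 98% at ρ = 0.7).

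Three stronger readings may tempt a reader, and the article supports none of them:

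- **That the trial is underpowered or 66 is wrong.** The sample size was set for an unadjusted comparison of post-treatment means and reproduces. A single contrast falls below that 81% only for change with ρ under 0.5, and ρ is not given. The plan's own test is an interaction over three visits with Bonferroni follow-up, whose power is not computed here.
- **That imbalance could shift the result by 2.15 points, or 60% of 3.57.** That is the range of the baseline difference. The shift in the estimate is ρ or (1 − ρ) times as large.
- **That the estimate is biased.** It is not, over repeated randomisation. The shift is conditional on the imbalance that happens to occur.

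**Conclusion.** The point holds as an available improvement in efficiency, not as a defect in validity. Whichever contrast section 4 intends, the planned estimate is less precise than a baseline-adjusted one: by 18% to 54% in variance for the change contrast, and by 10% to 96% for the week-4 difference, over correlations of 0.3 to 0.7. An imbalance at the edge of its 95% range would move the estimate by 0.64 to 1.50 points, depending on the contrast and the correlation.

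The direction of the gain does not depend on the unknown correlation, but its size does. The size also rests on the assumed equal SD at baseline and week 4.

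**What to change.** In section 4, before unblinding, choose one of two forms:

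1. Keep baseline CCS as a response and constrain the arms to a common baseline mean: drop the group main effect and keep group-by-visit terms at weeks 4 and 8 only.
2. Model CCS at weeks 4 and 8 only, with baseline CCS added to the covariate list.

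Baseline should not be both a response and a covariate in the same model. The secondary outcomes analysed with this mixed model should use their own baselines in the same way; the arithmetic above covers CCS only.

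The cost is one sentence. Baseline CCS is already scheduled for every participant, and no change to the sample size is needed.

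### The 80% power was derived for one week-4 comparison of CCS means, but the analysis section describes an interaction-conditional, Bonferroni-corrected procedure to which that figure does not carry over.

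*Protocol article*

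**What the plan says.** Four places in the protocol article bear on how the primary outcome is tested.

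- **Section 2.3 (Sample size calculation)** works "using a superiority test to compare two independent means", at alpha "0.05 (two-sided), and the statistical power was 80"%. The 66 participants are those "required to detect a statistically significant superiority in CCS scores between the two groups after the intervention". That is one visit and one comparison. The section does not mention an interaction, a within-person correlation, week 8 or a multiplicity correction.
- **Abstract, Methods**: "The primary outcome is the longitudinal change in the Chronic Constipation Severity Score (CCS) over time".
- **Section 2.7.1 (Primary outcome)** names the CCS but no visit. Table 2 schedules it at baseline, week 4 and week 8.
- **Section 4 (Statistical analysis)** sends repeated-measures data to a linear mixed model with group, time, their interaction and random intercepts. Post hoc comparisons, reported as least squares mean differences with 95% CIs, follow "If the group-by-time interaction was statistically significant", with Bonferroni correction. The number of comparisons is not given. A separate sentence in the same section reads: "Between-group comparisons were performed using the independent-samples t-test or Mann–Whitney U test, as appropriate".

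**The concern.** The contrast that was powered, the difference in mean CCS at the end of treatment, appears in section 4 only as a post hoc comparison. It is conditional on another test and then corrected for multiplicity. Read literally, no least squares mean difference or CI is promised when the interaction is not significant. The power statement belongs to an unconditional test at 0.05, and nothing in section 2.3 allows for the condition or the correction.

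Two things are at stake. The trial's stated power does not describe the analysis it sets out. And the estimate that a reader most needs could be left unreported because of the p-value of a different hypothesis, namely that the group difference is the same at all three visits.

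**Working it through.** **1. Reproduce the stated sample size.** Inputs from section 2.3: means 8.79 and 12.36, SDs 4.63 and 4.26, two-sided alpha 0.05, power 80%, dropout 20%.

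- Difference = 12.36 − 8.79 = 3.57.
- Pooled SD = √((4.63² + 4.26²)/2) = √19.79 = 4.449.
- Standardised effect = 3.57/4.449 = 0.802.
- Two-sample t-test (noncentral t): 25 per arm gives 79.4%, 26 per arm gives 81.0%, so 26 are needed.
- 26/0.8 = 32.5, so 33 per arm and 66 in total.

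The stated figure is right for a single unconditional comparison.

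**2. Effect of the Bonferroni correction alone.** The same t-test with 26 per arm has 71.9% power at 0.05/2 and 66.1% at 0.05/3.

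**3. Power of the interaction test alone.** With time categorical over three visits (assumed; 2 df) and compound symmetry with correlation ρ, the noncentrality is

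λ = (n/2) × Σ(δ_t − δ̄)² / (σ²(1 − ρ)), referred to F with 2 and 4n − 4 df.

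For n = 26, ρ = 0.5 and a sustained effect, δ = (0, 3.57, 3.57) and δ̄ = 2.38. The sum of squares is 2.38² + 2 × 1.19² = 8.50. So λ = 13 × 8.50/(19.79 × 0.5) ≈ 11.2, and power is 85%. With half the effect left at week 8, δ = (0, 3.57, 1.785), the sum of squares is 2 × 1.785² = 6.37, λ ≈ 8.4, and power is 73%. With no effect left at week 8 the sum of squares is again 8.50, and power is 85%.

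**4. Interaction followed by a week-4 comparison.** This was simulated with 26 complete cases per arm, SD 4.449, normal data, compound symmetry, no baseline difference and no gain from covariates. The correlation and the week-8 effect are assumptions, because the article gives neither. Entries are power (%) at ρ = 0.3 / 0.5 / 0.7.

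| Week-8 effect, % of week 4 | Interaction alone | Then raw week 4, uncorrected | Then raw week 4, corrected for 2 | Then week-4 change, corrected for 2 |
|---|---|---|---|---|
| 100 | 70 / 85 / 97 | 61 / 71 / 80 | 56 / 64 / 71 | 53 / 70 / 91 |
| 50 | 57 / 73 / 92 | 53 / 64 / 77 | 50 / 58 / 69 | 52 / 68 / 90 |
| 0 | 70 / 85 / 97 | 65 / 74 / 80 | 60 / 67 / 72 | 54 / 71 / 92 |

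The result depends a little on how the covariance is handled. An unstructured test of the two changes (Hotelling T²) followed by a plain t-test gives 53 / 62 / 71 and 48 / 57 / 67 for the first two rows of the raw corrected column. That is up to about 3 points lower. The rounded ranges in the verdict allow for this version.

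**The case against.** The strongest reply is that section 4 names no confirmatory test. A reader might infer that efficacy is decided by the interaction and then a corrected week-4 difference, so that the true power is roughly 48% to 71%. The article does not say so. Since the Abstract speaks of change over time and section 4 calls the comparisons post hoc, the interaction itself may be the primary test, with the visit contrasts as description. On that reading power exceeds 80% when the correlation is high: from about 0.5 with a sustained effect and about 0.6 with a half-retained one. The Bonferroni family is also undefined. If applied within a visit to two groups, it costs nothing. Whether the contrast is raw CCS or change from baseline is not stated either, and at ρ = 0.7 the change score gives about 90% where the raw score gives about 70%. All of this stands. It means that no single power figure, and not even a direction, can be assigned.

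A reader might also infer that the t-test or Mann–Whitney sentence sets up a rival primary analysis that could give an opposite verdict on the same data. That sentence names no outcome and no visit, and repeated-measures data are assigned to the mixed model. The reading is possible but not shown.

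Finally, sizing by a t-test and analysing by a mixed model is common, and an article may leave contrast coding to an analysis plan that is not shown. That excuses the missing detail. It does not excuse the rule that section 4 does state, which makes the estimate conditional on the interaction, nor the two accounts of the primary outcome in the Abstract and section 2.3.

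**Conclusion.** The mismatch holds. Section 2.3 powers one unconditional week-4 comparison of CCS. The Abstract defines a longitudinal outcome, and section 4 makes the least squares mean differences conditional and corrected. The 80% was not derived for that procedure.

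With 26 evaluable per arm, assumed correlation 0.3 to 0.7 and an assumed week-8 effect of 0 to 100% of week 4, power is about:

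- 55% to 97% for the interaction test alone;
- 51% to 80% for the interaction followed by an uncorrected raw week-4 comparison;
- 47% to 71% for the same, corrected for two comparisons;
- 51% to 92% for the interaction followed by a week-4 change-score comparison corrected for two.

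The spread shows how much is left open; it does not estimate a shortfall. A reader might conclude that 66 is too few. The documents do not support that, because 66 is correct for the comparison that section 2.3 describes.

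**What to change.** - In section 4, name the mixed-model between-group difference in CCS at week 4 as the single primary contrast. Test it at two-sided 0.05 and report it with its 95% CI whatever the interaction p-value.
- Make week 8 and the group-by-time interaction secondary, and confine any Bonferroni correction to a stated set of secondary comparisons.
- State that the t-test/Mann–Whitney route does not apply to the primary CCS analysis.
- Use the same primary-outcome wording, including the visit, in the Abstract and in sections 2.3, 2.7.1 and 4.

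This matches the primary analysis to the contrast for which the 66 was calculated. It costs wording in the protocol and analysis plan only, with no extra participants, visits or data. It should be settled before unblinding.
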